### Data collection and management

Data of the participants will be stored in the case report forms (CRFs), and the data will be input into the electronic CRFs by a specialized data reader. Data are managed by the China National Nuclear Corporation Hospital Data Management Committee. Data will be checked by the manager once a month. Therapists will not have access to the data during the study.

### Quality control

All the researchers will be trained with the trial methodology and APT technique before the first participant is included. During the trial process, the China National Nuclear Corporation Hospital Data Management Committee is in charge of quality control.

### Adverse events and safety assessment

The AEs included allergies to auricular plaster, swelling, and severe pain. When SAEs occur that pose a threat to the participant's safety, the study will be stopped immediately and the blinding will be canceled to preserve the participant's life. A detailed record of all AEs/SAEs will be kept during the course of the study, including the date, duration, treatment measures, and results.

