## Abstract

**Background:**

Children with autism spectrum disorders (ASDs) suffer from sleep disorders to a considerable degree; however, there is no safe and effective treatment available in clinical practice. The objective of the trial is to assess the clinical effectiveness of auricular plaster therapy (APT) in treating sleep disorders in children with ASD.

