As a part of traditional Chinese medicine (TCM), acupuncture is a vital component with a long history of treating diseases such as mental illness (28–30), cardiovascular disease and cerebrovascular disease (31), and tumor disease (32, 33). Auricular therapy is one treatment modality of acupuncture, which involves stimulating specific acupoints on the outer ear in an effort to promote health and wellbeing (34). As a form of auricular therapy, auricular plaster therapy (APT) is composed of a round and hard cowherb seed and a sticky adhesive tape with a size of 0.5 cm ^*^ 0.5 cm (35). Due to the non-invasive, safe, and convenient nature, once auricular plaster is affixed by the doctor, patients themselves can press and stimulate the points at the convenience of their own time. Although the mechanism by which APT treats insomnia is not fully understood, numerous studies have indicated that APT helps relieve insomnia by modulating neurotransmitter activity and affecting the nervous system (36). Several systematic reviews and meta-analyses of APT show that APT appears to be an effective and safe treatment for patients with primary insomnia (37–41). In the most recent study, a retrospective cohort study of APT treatment of 84 patients with coronavirus disease 2019 (COVID-19) with insomnia showed that APT was effective in alleviating insomnia and anxiety (42). Another RCT of 50 patients receiving methadone maintenance treatment (MTT) showed that APT combined with electroacupuncture could significantly improve sleep quality, sleep latency, and increase MMT adherence (43). In addition, the application of APT has also been extended to the treatment of pain management (44, 45), postoperative rehabilitation (46), attention deficit (47), primary dysmenorrhea (48), and other conditions. Nevertheless, to our knowledge, there have been no RCTs evaluating the efficacy of APT for sleep disorders in children with ASD. Given that APT is effective in treating insomnia in adults, we aim to test the safety and efficacy of auricular plaster therapy for the treatment of sleep disorders in preschool children with ASD, which may provide a viable alternative treatment method.

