## Methods and analysis

### Study design

This study is a parallel-design, patient-assessor blind randomized controlled trial (RCT) comparing the use of APT with sham APT. The recruitment of participants will take place from 1 August 2021 to 31 December 2022. The program will enroll autistic preschoolers with sleep disorders who will be assessed at the Sichuan Beidouxing Rehabilitation Service Center as well as three other community hospitals (Fuqin Community Health Service Center, Tiaodenghe Community Health Service Center, and Xianqiao Community Health Service Center). The clinical trial was registered on CHiCTR.org.cn (ChiCTR2100048257) before we enrolled our first participant, and the study was approved by the Second Affiliated Hospital of Chengdu Medical College, China National Nuclear Corporation 416 Hospital Ethics Committee (KJ2021012).

Eligible participants will be randomly assigned to the APT group or the sham APT group on a 1:1 basis. An observation period of 120 days will be conducted, including a 30-day treatment period and a 90-day follow-up period. Children will receive APT continuously for 1 month. Assessments will be conducted at baseline as well as 10, 20, 30, 60, 90, and 120 days after randomization. The study flowchart is shown in Figure 1, and the schedule of the trial is shown in Table 3.

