	**Study period**							
	**Enrollment**	**Allocation**	**Post-allocation**				**Follow-up period**		
**Timepoint (days)**	**-7**	**0**	**1**	**10**	**20**	**30**	**60**	**90**	**120**

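### The schedule table stops adverse event assessment at day 30, while the text promises a record of all events over a study that runs to day 120

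*Protocol article*

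**What the plan says.** The section on adverse events and safety assessment in the protocol article makes a broad promise: "A detailed record of all AEs/SAEs will be kept during the course of the study". It adds that each record will cover when the event occurred, how long it lasted, what was done and how it ended. The same section opens with a short list: "The AEs included allergies to auricular plaster, swelling, and severe pain".

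The study design section sets the length of the study: "An observation period of 120 days will be conducted, including a 30-day treatment period and a 90-day follow-up period". It also gives the contact times: "Assessments will be conducted at baseline as well as 10, 20, 30, 60, 90, and 120 days after randomization".

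Table 3 lays out those times in columns. Its adverse event row is marked at days 10, 20 and 30 and is blank at days 60, 90 and 120. The rows for the Children's Sleep Habits Questionnaire (CSHQ) and the Autism Behavior Checklist (ABC) are marked at all three follow-up times.

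On purpose, the introduction says "we aim to test the safety and efficacy of auricular plaster therapy", whereas the abstract names only effectiveness: "The objective of the trial is to assess the clinical effectiveness of auricular plaster therapy (APT".

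**The concern.** The text and the schedule give different answers to one question: until when are adverse events collected? The text implies day 120, and the table ends at day 30. Staff who work from the schedule would have no prompt to ask about events in follow-up, although the child is being assessed on those days anyway.

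Two kinds of event are exposed. One is an event that begins after the last plaster has come off. The other is an event still present at day 30, whose duration and outcome the text promises to record but for which no later check is scheduled. If such events reach the record only when a family happens to mention them, capture need not be the same in the two arms. The safety comparison would then be less secure than the article's safety aim suggests.

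**Working it through.** No power or sample size figure is involved. The check is a reading of Table 3 against the text, followed by a count.

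**Is the table read correctly?** The column headings are "Timepoint (days) -7 0 1 10 20 30 60 90 120". The same column positions were applied to the other assessment rows:

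| Row in Table 3 | Days marked | Agrees with the text? |
|---|---|---|
| CSHQ | 1, 10, 20, 30, 60, 90, 120 | Yes, taking day 1 as baseline |
| ABC | 1, 10, 20, 30, 60, 90, 120 | Yes, same schedule as CSHQ |
| Polysomnography | 1, 30 | Yes: baseline and end of treatment |
| Adverse events | 10, 20, 30 | No: the text says the whole study |

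Three rows fall where the text puts them, so the blanks in the adverse event row are unlikely to come from text extraction.

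**Count of assessments.**
- After baseline there are six: days 10, 20, 30, 60, 90 and 120. Adverse events are marked at three of the six.
- In follow-up there are three: days 60, 90 and 120. Adverse events are marked at none of the three.

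**Coverage of exposure.** Plasters are applied for 30 consecutive days and changed daily by the acupuncturists (Interventions section). The last adverse event check is at day 30, so the scheduled checks cover 30 of 30 treatment days. The stretch without a scheduled check is 120 − 30 = 90 days, all of it after treatment.

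**The list of events.** The sentence naming three reactions says that adverse events included them, and the section then promises to record all events. Read together, the three are most naturally examples. The drop-out criteria agree with this: they treat severe adverse events and plaster allergy as separate reasons. The wording still leaves scope open in one respect, because pain is listed only when severe. One clarifying sentence would settle this.

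**The case against.** The strongest reply is that both statements can hold. Table 3 shows scheduled assessments, while the text describes continuous recording. Checks during treatment, with later events written down as they arise, would satisfy both. This stands to the extent that no loss of data is demonstrated. However, the article describes no route for reports after day 30, so the reader cannot tell whether this is what is meant.

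A second reply is that the article condenses a fuller protocol, where the definition, grading and collection window of adverse events would normally be found. That is fair for definition and grading, and their absence here is not a fault. It does not remove a disagreement between two statements that the article does make.

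A third is that safety is peripheral: the abstract's objective leaves it out, and adverse events are neither a primary nor a secondary outcome. This lowers the weight of the point, but the introduction still states the aim.

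Three stronger readings might be inferred, and the documents do not support them.
- *Events outside the three named reactions would go uncounted.* Nothing says so, and the promise covers all events. Worsening sleep or behaviour would in any case show in the CSHQ and ABC scores up to day 120, though not labelled as an adverse event.
- *Three quarters of the risk period is unobserved.* The fraction 90/120 = 75% is calendar time. Allergy, swelling and pain from pressing are tied to a plaster being in place, and all of that time is covered.
- *Event counts will certainly be too low.* No figure in the article shows how many events would be missed, if any.

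**Conclusion.** The mismatch is real and limited. The schedule ends adverse event assessment at day 30, the text promises a record of all events during the study, and none of the three follow-up assessments carries a check. Most plaster reactions should still be captured, because the checks span the full treatment period. The gap concerns late-onset events and events unresolved at day 30, and its size in events cannot be derived from the article.

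This rests on two assumptions: that the course of the study means the 120-day observation period, and that no reporting route for follow-up is set out in a full protocol not shown here. If such a route exists, the point reduces to making Table 3 agree with it.

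**What to change.** Make Table 3 and the adverse event section agree:

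1. Add adverse event marks at days 60, 90 and 120, so that both arms are asked about new and unresolved events on the same occasions.
2. State in the adverse event section that plaster allergy, swelling and severe pain are examples, and that events of any kind or severity are recorded up to day 120, in line with the promise already made there.

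This takes three marks in one table row and one sentence. The contacts already take place for the CSHQ and ABC, so no new visit is needed. The price is slightly more data entry and possibly a less favourable adverse event count.

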### Statistical analysis

An analysis of the data will be conducted using SPSS (Version 24, IBM, Armonk, New York, USA). Data will be analyzed on the basis of intention-to-treat (ITT) and per-protocol (PP) analysis. The ITT analysis includes all the participants who received at least one acupuncture treatment and one assessment of the primary outcome. The PP analysis includes participants who complete the trial. Continuous data will be expressed as medians and interquartile ranges. Categorical data will be presented as numbers and percentages. Continuous variables will be compared using the independent-sample *t-*test or the Mann–Whitney *U*-test. Categorical variables will be compared with the chi-squared test or Fisher's exact test. Missing values will be addressed by multiple imputations, having appropriately explored the missingness mechanism and in accordance with good practice. Two-sided *P* < 0.05 will be considered significant.

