**Method:**

This is a single-center, patient-assessor blind, randomized controlled trial. A total of 44 preschool children with sleep disorders with ASD will be included in this study. Eligible participants will be randomly assigned to either the auricular plaster group or the sham auricular plaster group in a 1:1 ratio. Participants in the different groups will receive APT or sham APT, respectively, for a total of 30 sessions over 30 days. The primary outcome includes the Children's Sleep Habits Questionnaire (CSHQ), while secondary outcomes include the Autism Behavior Checklist (ABC) and polysomnography (PSG) for total sleep time, sleep latency, awakening duration, and sleep structures. The CSHQ and ABC will be assessed at baseline, 10, 20, 30, 60, 90, and 120 days after randomization, whereas PSG will be assessed at baseline and 30 days after randomization. The follow-up period will be scheduled to be 60, 90, and 120 days after randomization.

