### Interventions

Based upon clinical experience in APT for sleep disorders and characteristics of TCM treatment of sleep disorders in children with ASD, the acupoints of the heart (CO15), Jiaogan (AH6a), Shenmen (TF4), subcortex (AT4), kidney (CO10), and spleen (CO13) are chosen in this study (56). The locations of the auricular points can be found in Table 4 and Figure 2. Both groups will be treated with APT for 30 consecutive days. Before participating in the trial, the acupuncturists qualified as Chinese medicine practitioners have at least 3 years of clinical experience, and successfully passed a relevant test, including auricular point positioning, auricular point duration, and participant attention. The auricular plaster (Heshi MedTech Co., Ltd., Hengshui, Hebei, China) consists of cowherb seeds wrapped in a tape of 0.5 cm ^*^ 0.5 cm. Participants in the sham APT group will only be treated with the same shape as auricular plaster without cowherb seeds. To increase compliance, we also manufacture special auricular plaster, which is covered with cartoon stickers. Acupuncturists will change the auricular plaster application for participants every day. Participants are not allowed to take any therapeutic drugs (e.g., melatonin) for sleep disorders during the study.

**Table 4 T4:** Locations of auricular points.

**Auricular point**	**Location**
Heart (CO15)	Located at the middle of the concha
Jiaogan (AH6a)	Located at the junction of the front end of the lower part of the antihelix and the inner edge of the helix
Shenmen (TF4)	Located at the upper of the posterior third of the triangular fossa
Subcortex (AT4)	Located at the medial side of the antitragus
Kidney (CO10)	Located at the rear of the lower part of the antihelix
Spleen (CO13)	Located at the posterior upper part of the concha

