#### Auricular plaster group

Based on conventional rehabilitation training for children with ASD, children in the auricular plaster group will be provided with APT. Children themselves or their parents are told to press the auricular plaster three times a day (8 a.m., 2 p.m., half an hour before sleep at night), each point for 30–60 s, so that the auricular point produces an acidic and swollen sensation that can be tolerated by the children.

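### The set called ITT is a modified ITT set that depends on events after allocation, and the plan does not say whether the baseline CSHQ meets its assessment condition

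*Protocol article*

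**What the plan says.** All of the relevant rules stand in the Statistical analysis section of the protocol article.

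- Two analyses are planned: "Data will be analyzed on the basis of intention-to-treat (ITT) and per-protocol (PP) analysis".
- The first set is defined thus: "The ITT analysis includes all the participants who received at least one acupuncture treatment and one assessment of the primary outcome".
- The second is defined thus: "The PP analysis includes participants who complete the trial".
- Missing data: "Missing values will be addressed by multiple imputations, having appropriately explored the missingness mechanism".

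No other section defines a set of all randomised children or says that children are analysed in the arm assigned.

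Four other places bear on the definitions. Randomization and blinding says that the allocation is sent to acupuncturists who cannot be blinded. Table 3 puts allocation on day 0 and the first CSHQ in the day-1 column. The abstract and the intervention sections describe treatment as planned: "for a total of 30 sessions over 30 days", and in the APT arm only, "Children themselves or their parents are told to press the auricular plaster three times a day". The Interventions section adds: "Participants are not allowed to take any therapeutic drugs (e.g., melatonin) for sleep disorders during the study".

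**The concern.** An intention-to-treat set takes its value from being fixed at randomisation: nothing that happens later can change who is compared. The stated rule has two conditions, a treatment received and a CSHQ assessment made, and both are met or missed after the arm is known to the person giving the treatment.

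Loss need not be equal between arms. APT families press seeded plasters three times a day; sham families have plasters without seeds and are not told to press. Allergy to the plaster is a drop-out reason, and swelling and severe pain are listed adverse events. The adhesive is on the ear in both arms, but the seed and the pressing are not. If APT children who tolerate the plaster badly leave early and would have done worse than the rest, removing them flatters APT.

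Two further problems follow from the wording. The single assessment is not said to be after baseline, so two analysts could build different sets from the same data. And a report that uses the ITT label would misdescribe its population.

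The per-protocol set is a lesser matter. As written it turns on completion, with no reference to the planned sessions, the pressing or the ban on sleep drugs.

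**Working it through.** **Step 1. What each reading of the ITT rule removes.**

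| Child | All randomised | Rule, baseline CSHQ counts | Rule, later CSHQ required |
|---|---|---|---|
| Never treated | in | out | out |
| Treated, day-1 CSHQ only | in | in | out |
| Treated, at least one CSHQ from day 10 on, later gaps | in | in | in |

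The rule differs from ITT under both readings, because never-treated children are always lost. The readings part on the second row. For that child imputation is possible from the baseline CSHQ and arm, but under the stricter reading the child has left before imputation begins. For the third row imputation works as planned under either reading.

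**Step 2. Possible size.** The plan states no figure on this point, so there is none to reproduce. The following is an illustration.

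Inputs from the Sample size section: 22 children per arm; reference CSHQ mean 48.5 and SD 9.7; assumed APT mean after treatment 40; dropout 10%. Assumptions not in the documents: excluded APT children stay at 48.5, the other APT children average 40, and no sham child is excluded. The section does not state a sham mean; taking it as 48.5 gives the difference 48.5 − 40 = 8.5 used below for scale.

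With k of 22 APT children excluded, the mean of the whole arm is [k × 48.5 + (22 − k) × 40] / 22 = 40 + (k/22) × 8.5. The restricted set gives 40. The shift is therefore (k/22) × 8.5:

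| k | Share of arm | Shift (points) | Share of 8.5 |
|---|---|---|---|
| 1 | 4.5% | 0.39 | 4.5% |
| 2 | 9.1% | 0.77 | 9.1% |
| 3 | 13.6% | 1.16 | 13.6% |
| 4 | 18.2% | 1.55 | 18.2% |

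Changing the assumed gap: if excluded children are 0.5 to 1 SD worse than the others, the shift is (k/22) × gap × 9.7. The smallest case is (1/22) × 0.5 × 9.7 = 0.22 points (3% of 8.5) and the largest (4/22) × 1 × 9.7 = 1.76 points (21%).

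Scale of k: planned dropout is 0.10 × 22 = 2.2 children per arm. So k = 2 needs almost all of one arm's planned dropout to occur before the set conditions are met, and k = 4 is nearly double the planned rate.

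**Step 3. What imputation would recover.** Standard imputation from arm and baseline CSHQ draws on the APT children who were observed. For excluded children with similar baselines it gives about 40, so the imputed arm mean stays near 40 and most of the shift remains. A delta adjustment adds (k/22) × delta to the arm mean. With k = 2 and delta = 8.5 that is 0.77, giving 40.77, the mean of the whole arm in this scenario.

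**Step 4. The per-protocol rule beside the treatment plan.** The plan sets 30 sessions, pressing in the APT arm and no sleep drugs. The rule names none of these and gives only completion, which is not itself defined.

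**The case against.** The strongest reply is that the rule excludes few children. Its words ask for one assessment, not a post-baseline one. With a CSHQ on day 1 and acupuncturists applying the plasters from the start, a treated child nearly always qualifies, and only the never-treated are lost. This stands as a limit on size. It does not make the set ITT, and it rests on a reading that the text does not settle.

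A reader might infer that the rule defeats the multiple imputation. The documents do not support that: CSHQ is scheduled at baseline and six later visits, and any child in the set with later gaps can be imputed. Imputation is curtailed, and under the stricter reading only.

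A reader might also take the illustrated shift as an estimate of bias, or as the gain from imputing all randomised children. It is neither. It places every exclusion in the APT arm and makes each excluded child a complete non-responder. Equal exclusions of similar children in both arms would largely cancel, and Step 3 shows that ordinary imputation would leave most of the shift.

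Finally, a reader might conclude that the per-protocol set certainly keeps a child who took melatonin or missed most sessions, and drops an adherent child who missed only day 120. The article does not say what counts as completing the trial. Detailed deviation criteria are commonly left to an analysis plan, which is not shown here. What stands is that the definition, as published, is that of a completer set.

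**Conclusion.** The point holds in a limited form. The article states a definition of ITT that is not ITT: it conditions on two events after allocation, in a trial with unblinded acupuncturists, and no all-randomised set stands beside it. Because the definition is stated, this is not a detail deferred to an analysis plan. The uncertainty over the baseline CSHQ is a second, separate defect in the same sentence.

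The effect on the result is unknown and probably small: about 0.4 to 1.5 points on the APT mean for 1 to 4 exclusions under the assumed values, less if exclusions are balanced, and close to nothing if every child is treated and the baseline CSHQ counts. In an arm of 22, though, each child is 4.5% of the comparison. It should be fixed, but it does not invalidate the design. The per-protocol wording is secondary and calls for a clearer label or definition.

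**What to change.** 1. Define the ITT set as all randomised children, analysed in the arm assigned.
2. Apply the multiple imputation already planned to missing CSHQ values, with baseline CSHQ and arm in the imputation model, including children with no post-baseline value.
3. Add a delta-adjusted or worst-case sensitivity analysis for imputed children, since imputation under the usual assumptions cannot show what happens if those who left did worse.
4. Keep the present rule, if wanted, as a supportive set labelled modified ITT, and state whether a post-baseline CSHQ is required.
5. Either call the second set a completer set, or define per-protocol by adherence to the assigned sessions and absence of major deviations such as use of prohibited sleep drugs. State the criteria before unblinding.

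The cost is wording and a modest amount of extra analysis; no new data are needed. The article reports recruitment under way at submission, so the definitions should be settled and dated before the allocation is disclosed to the analysts.

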### Outcome measurements

#### Primary outcome

The primary outcome is the Children's Sleep Habits Questionnaire (CSHQ) (57), which contains seven items, including bedtime, sleep habits, sleep behavior, night wake, morning wake, daytime sleepiness, and total sleep time, with different items representing different sleep problems. Higher scores indicate a greater problem with sleep (58). The CSHQ will be evaluated at baseline and 10, 20, 30, 60, 90, and 120 days after randomization. Sleep assessment ranges from 1 month prior to baseline, every 10 days in the treatment period, and every 30 days in the follow-up period.

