### Sample size

A multisite case-control study which including 552 sleep problem in two to five children with ASD showed that the mean score of the CSHQ for ASD children was 48.5, and the standard deviation (SD) of CSHQ was 9.7 (62). Another study utilizing scalp acupuncture to treat sleep disorders in children with ASD showed a significant improvement in total CSHQ scores of 38 after treatment (63). Based on these two studies, we assume that the mean CSHQ score of children with ASD after receiving APT treatment is 40, and the SD in the auricular plaster group and sham auricular plaster group was 9.7. Assuming a significance level of 0.05 and a study power of 0.8 with a 10% dropout rate, 44 participants were required for this study, with 22 participants in each group. The sample size was calculated using power analysis and sample size (Version 11.0.7, NCSS, Englewood, New Jersey, USA).

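### The stated between-arm test for the CSHQ names no baseline covariate; it is valid, but ANCOVA on the baseline already collected would give this 44-child trial more power

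*Protocol article*

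**What the plan says.** In the protocol article, under Statistical analysis, one sentence covers all continuous outcomes, the primary one included: "Continuous variables will be compared using the independent-sample" t-test or the Mann–Whitney U-test, judged at a two-sided 5% level. The article mentions no covariate, ANCOVA, mixed model or change score.

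Baseline values will be available. Under Primary outcome, "The CSHQ will be evaluated at baseline and 10, 20, 30, 60, 90, and 120 days after randomization". The study schedule and Secondary outcomes give ABC the same visits, and PSG a recording at baseline and at the end of treatment.

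Under Sample size, a cited case-control study supplies the reference value: "the mean score of the CSHQ for ASD children was 48.5". The trial then assumes that "the mean CSHQ score of children with ASD after receiving APT treatment is 40" and that "the SD in the auricular plaster group and sham auricular plaster group was 9.7". With alpha 0.05, power 0.8 and 10% dropout, the article arrives at 44 children, 22 per arm. Its Discussion lists the small sample as a limitation.

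**The concern.** When an outcome is also measured before treatment, part of its between-child variation can be predicted from the baseline value. A two-group test on the follow-up score leaves that part in the error term. ANCOVA removes it, cutting the residual variance by the square of the baseline–outcome correlation.

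This matters more here than in a large trial. With about 20 evaluable children per arm, the plan is slightly short of its own 80% target, so precision that costs nothing is worth taking. Because the article names the test, a later analysis plan that adopted ANCOVA would be replacing a stated method, not filling a gap. At stake are the power of the primary comparison and the width of its confidence interval, not its validity.

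**Working it through.** **Inputs from the Sample size and Statistical analysis sections**
- Mean after APT: 40. Comparator mean: 48.5, an inference, since the text does not label it as the sham mean. Difference 48.5 − 40 = 8.5.
- SD 9.7 in both arms; two-sided alpha 0.05; power 0.80; dropout 10%; 22 per arm.
- Evaluable children per arm: 22 × 0.9 = 19.8, taken as 20.
- Baseline–outcome correlation r: not given. Assumed values 0.2, 0.3, 0.5 and 0.7.

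**The plan's own figure**

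The normal approximation gives 2 × (1.96 + 0.842)² × 9.7² / 8.5² = 20.4, so 21 per arm. The noncentral t calculation gives 22 per arm. The stated 44 therefore equals the t-test size before any dropout allowance. Dividing by 0.9 gives 24 per arm (48 in all) from the normal figure, or 25 per arm (50 in all) from the t figure. I could not reproduce 44 with dropout included. That is a separate matter; here it only shows that there is no spare power.

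**Unadjusted t-test**

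Standard error = 9.7 × √(2/20) = 3.07. Noncentrality = 8.5 / 3.07 = 2.77 on 38 degrees of freedom. Power is 0.77, and the 95% CI half-width is 2.024 × 3.07 = 6.2 points. With all 22 per arm, power is 0.81.

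**ANCOVA on baseline**

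Residual SD = 9.7 × √(1 − r²), with 37 degrees of freedom. At r = 0.5: 9.7 × √0.75 = 8.40; standard error 8.40 × √(2/20) = 2.66; noncentrality 8.5 / 2.66 = 3.20; power 0.88.

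**t-test on change, if that was intended**

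Assuming the same SD at both visits, SD of change = 9.7 × √(2(1 − r)). At r = 0.3: 9.7 × √1.4 = 11.48; power 0.63.

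| r | ANCOVA residual SD | ANCOVA power | ANCOVA 95% CI half-width | SD of change | Change-score power |
|---|---|---|---|---|---|
| 0.2 | 9.50 | 0.79 | 6.1 | 12.27 | 0.57 |
| 0.3 | 9.25 | 0.81 | 5.9 | 11.48 | 0.63 |
| 0.5 | 8.40 | 0.88 | 5.4 | 9.70 | 0.77 |
| 0.7 | 6.93 | 0.97 | 4.4 | 7.51 | 0.94 |

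All rows use 20 per arm and a difference of 8.5; the unadjusted comparison is 0.77 and 6.2 points. Change scores are worse than raw scores below r = 0.5, equal at 0.5 and better above it.

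One refinement: the ANCOVA figures assume balanced baselines. With a roughly normal baseline, chance imbalance inflates the variance on average by 1/(2n − 4) = 1/36, or 2.8%. At r = 0.2 the net variance ratio is 0.96 × 1.028 = 0.99, so almost nothing is gained. At r = 0.5 it is 0.75 × 1.028 = 0.77, so most of the gain remains.

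**The case against.** The strongest reply is that nothing is wrong with the stated test. In a randomised trial an unadjusted comparison controls type I error, and chance baseline imbalance is already reflected in its standard error. It also fits the sample size, which uses scores and their raw SD. All of that stands: this is an improvement in efficiency, not the correction of an error.

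The size of the gain is also open. The correlation could be low: the CSHQ covers a month before baseline but ten-day spans during treatment, and entry requires a diagnosed sleep disorder, which may narrow the baseline range. This stands too, and is why the range starts at 0.2.

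A reader might infer more than the article supports:
- *That raw scores are certainly what will be tested.* The text does not say whether the variable is the score or its change, and the Discussion speaks of the CSHQ before and after treatment. The raw SD in the sample size makes scores the likelier reading, but that is an inference. The change-score reading does not remove the point, as the table shows.
- *That the trial will report no treatment difference or confidence interval.* The statement "Continuous data will be expressed as medians and interquartile ranges" describes how data are summarised, not the contrast between arms. A t-test yields a mean difference with its interval, and such reporting is commonly left to the analysis plan.
- *That the open choice between the two tests, or its fit with the sentence "Missing values will be addressed by multiple imputations", is a defect in itself.* The rule for choosing and the method of pooling are details that a condensed article usually leaves to the full plan. The pooling question arises only if the rank test is used.

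**Conclusion.** The point holds as a recommendation on efficiency. The article names an unadjusted two-group test for outcomes whose baselines are all collected, and a baseline-adjusted model would serve the trial better. At 20 per arm, a difference of 8.5 and an SD of 9.7, power would rise from about 0.77 to between 0.79 and 0.97 for r from 0.2 to 0.7. The benefit is negligible at the bottom of that range and large at the top.

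This rests on three assumptions: that 48.5 is the comparator mean, that about two children per arm are lost, and that r lies in the range shown. The direction is secure except at very low correlations; the size is not, because the protocol gives no correlation. The planned test remains valid.

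**What to change.** Before unblinding, name as the primary analysis an ANCOVA of CSHQ total, at whichever time point is chosen as primary (for example day 30, the end of treatment), on treatment arm with baseline CSHQ as covariate. Report the adjusted mean difference with its 95% confidence interval. Use the same model for ABC and the PSG variables, each with its own baseline, and keep the Mann–Whitney test as a sensitivity analysis. A mixed model across visits is a possible alternative, but it handles repeated visits and missing data differently, so one model should be named as primary.

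The cost is one degree of freedom and a change to the analysis wording. No extra data are needed. As the method is in the published protocol and recruitment was under way at submission, the change should be recorded as a dated amendment.
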